#### In-Depth Interviews and Cross-sectional Surveys

In-depth interviews and cross-sectional surveys began at the conclusion of the 18-month EMERALD cohort. In total, thirty 45- to 60-minute in-depth interviews will be conducted with intervention cohort members who did (n=15) and did not (n=15) visit the SPARC center, and 15 interviews will be completed with SPARC center staff and outreach workers. The EMERALD cohort participants receive a US $25 prepaid Visa debit card for completing the interview; however, SPARC staff are not paid for participation. Interviews with intervention area cohort participants assess program fit, facilitators, and barriers to access of SPARC center services. Respondents are asked about the convenience of hours of operation, center location, staff, and services. Participants are also asked what they liked or disliked about the program and recommendations for additional services. Interviews with SPARC staff examine facilitators and barriers to the success of SPARC and how to improve services and reach.

We are further assessing the intervention’s reach (eg, peer educator contact) through a cross-sectional survey at 18 months among cisgender women aged ≥18 years (n=100) recruited from the intervention areas. Surveys are interviewer administered; take approximately 10 minutes to complete; and consist of questions regarding sex work history, knowledge, and utilization of SPARC services. Participants receive a US $5 prepaid Visa card for completing the cross-sectional survey.

#### Study Monitoring

The EMERALD study team has several key roles: the principal investigator and co-investigators, study director, field supervisor, field staff, and data manager. Investigators and the study director are responsible for protocol development and the oversight of the study progress. Field staff are responsible for data collection, and the data manager monitors and analyzes all study data to ensure that the data are of the highest quality. EMERALD investigators and the research team meet weekly to obtain feedback from field staff regarding study protocols and to discuss study progress. On the basis of staff feedback, data collection protocols are updated and subsequently sent to the JHBSPH IRB for approval. Any adverse events are reported to the JHBSPH IRB within 10 days, as required. Annual progress reports are also submitted to the study sponsor and to the JHBSPH IRB, documenting study progress. Finally, an independent and external data safety monitoring board comprising individuals with relevant expertise provides oversight and monitors study progress.

### Statistical Analysis

The principal analytic approach will center on generalized linear models for the individual data, with variance components that reflect the potential correlations among FSWs recruited from the same area and between repeated measurements from the same individual at baseline and follow-up visits [55,56]. The main covariate of interest is the intervention indicator. To address aim 1, we consider illicit drug use and irregular condom use as the primary behavioral endpoints.

The effect of the intervention will be assessed with a random effect hierarchical logistic model, with the intervention indicator, time, and their interaction as the main explanatory variables. To adjust for possible imbalances between the 2 areas, we will adjust for baseline confounding factors, including age, length of sex work, and number of sexual partners. The intervention effect will be assessed by comparing time trends in the intervention group with the time trend in the comparison group, as captured by the interaction term. The model will be expanded to include additional demographic covariates and time-dependent indicators of events such as arrest, homelessness, use of health services, or exposure to other prevention activities that are unrelated to the study. Aim 1 also seeks to evaluate the association between the degree of exposure to the intervention and observed behavioral changes. We will explore models that include as covariates participation or exposure to specific intervention components (ie, receiving medical care, drug treatment referral, and legal aid). On the basis of the literature, an 18-month follow-up should be sufficient to document meaningful changes in study outcomes, given the extent of the intervention [57].

For the primary biological endpoint of HIV and STI incidence, we will initially estimate cumulative incidence rates in both the intervention and comparison participants as a binary outcome and construct confidence intervals, accounting for the correlation structure because of nesting in geographic recruitment areas. The intervention’s effect will be assessed using an unadjusted random effect logistic model, with the intervention indicator as the only explanatory variable. The model will be expanded to include baseline covariates, such as demographic characteristics, history of sex work, and baseline risk behaviors (ie, condom use). A more detailed analysis will employ person-time methods with Poisson regression models to allow for time-updated covariates measured over time. Those lost to follow-up will contribute time-at-risk until the time of their last visit.

Finally, to evaluate the reach of the intervention, we will estimate SPARC involvement of FSWs in the independent cross-sectional survey at the 18-month follow-up period. We will also compare this sample with the FSW cohort at 18 months to assess their comparability or differences regarding demographic and risk profiles using logistic regression with group membership as the outcome variable.

To address aim 2, we will first describe changes over time in various sociostructural (ie, social cohesion and stigma) and structural vulnerability (eg, housing stability) indicators. We will then contrast these trends between the intervention and comparison groups. Social cohesion, social participation, and collective action will be analyzed as aggregate measures, the form of which will be determined by exploratory analysis. Specific models for formal statistical comparisons will be developed based on exploratory analysis, identifying both the distributional properties of the indicators and the shape of changes over time. To assess the association of these changes with the study’s primary endpoints, we will develop random effects logistic models, where the changes in structural indicators at each visit compared with baseline will be the main explanatory factors, in addition to the intervention indicator. The random effects will reflect the nesting of observations within the recruitment area and person over time.

To address aim 3, we will carry out mediation analyses evaluating the contribution of intermediate endpoints that were targeted by the intervention on the primary study outcomes. These include sociostructural factors (eg, stigma and social cohesion) and behavioral outcomes (illicit drug use and irregular condom use). We will have limited power to perform a definitive mediation analysis, but we plan to run detailed descriptive analyses and develop initial models to evaluate potential mediators that could be later validated in a larger study. The analysis will be based on recent developments in mediation analysis that extend earlier results to outcomes that are binary, such as irregular condom use. Specifically, the mediation formula proposed by Pearl [58] and the general framework for causal mediation analysis by Imai et al [59] will be adopted. Full data analysis and power calculation details are available from the senior author upon reasonable request.

To address aim 4, interviews with staff, FSWs, and peer educators will be entered and managed separately using ATLAS.ti software (Scientific Software Development GmbH). Coding will reduce the data to manageable units of information that cover broad and general categories. Themes that emerge from the data will be analyzed using a grounded theory approach [60,61]. A total of 2 coders will conduct open coding on 3 transcripts to develop initial coding schemes. After discussion and development of a combined draft scheme, 2 additional interviews will be coded to inform the final coding scheme. Discrepancies will be discussed with the interviewers and the primary investigator. Through weekly analysis meetings, a team approach to data analysis will be employed, whereby different researchers provide feedback on emerging interpretations and check emerging categories against the raw data. An audit trail will ensure the trustworthiness of findings, gather input from multiple perspectives, and enhance reliability [62].

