The need for US-based interventions is underscored by results from our recently completed SAPPHIRE (Sex Workers and Police Promoting Health in Risky Environments) study, a prospective observational cohort study of cisgender (n=250) and transgender (n=63) street-based FSWs in Baltimore [38-46]. Cisgender FSWs showed elevated rates of structural vulnerabilities, including housing instability, food insecurity, limited education, and criminal justice involvement, and injection and noninjection drug use, compared with similarly aged peers. Structural vulnerabilities were associated with high baseline prevalence estimates of STIs, including HIV (5%), chlamydia (10%), and gonorrhea (12%) [40], and the incidence of chlamydia and gonorrhea was 13.7% and 18.2%, respectively, over 12 months [43]. Participants also reported frequent interactions with police and a high prevalence of police, intimate partner–, and client-perpetrated violence [38,44].

Building on these results, we aim to develop and evaluate the effectiveness of a community-based combination HIV and STI prevention intervention in Baltimore, Maryland, to include a range of biomedical (eg, HIV and STI testing and counseling, Title X–funded reproductive health, HIV treatment, drug treatment, and primary care referrals), behavioral (eg, HIV and STI risk reduction education), and structural (eg, financial literacy, legal aid, and housing referrals) services provided through SPARC (Sex Workers Promoting Action, Risk Reduction, and Community Mobilization), a drop-in center and comprehensive outreach program. This study uses a structural determinants framework (Figure 1) to understand the complex and multifaceted nature of FSWs’ HIV risk [47]. This framework is informed by fundamental cause theory, which argues that fundamental causes (eg, poverty) have a greater impact on health than behavioral risks, and empowerment theory, which links social participation to increased social cohesion [34,48,49]. In this paper, we describe the design of the EMERALD (Enabling Mobilization, Empowerment, Risk Reduction, and Lasting Dignity) study, which evaluates the impact of the SPARC intervention. We also detail the SPARC intervention aims, components, and lessons learned during implementation. All study procedures were approved by the Johns Hopkins Bloomberg School of Public Health Institutional Review Board (JHBSPH IRB).

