### Aims and Hypotheses

The EMERALD study, detailed below, aims to examine (1) the effect of intervention exposure on HIV and STI risk behaviors (eg, drug use and unprotected sex) and HIV and STI cumulative incidence over time in FSWs in the intervention group compared with those in the comparison group, (2) how sociostructural (eg, social cohesion and stigma) and structural vulnerability (eg, financial and housing stability) indicators change and are associated with the biological and behavioral outcomes over time in FSWs in the intervention group compared with those in the comparison group, (3) the role of these indicators as mediators of the intervention effect on study outcomes, and (4) the implementation of the intervention through qualitative (eg, in-depth interviews) and quantitative (eg, assessment of program fit, reach, and cost, and facilitators and barriers to utilization measures).

The SPARC center and associated outreach is the intervention being evaluated by the EMERALD study, which consists of an 18-month longitudinal cohort study comprising intervention (n=224) and control (n=161) participants, a cross-sectional survey to assess program reach (n=100), and in-depth interviews (n=45) to assess SPARC implementation. We hypothesize that addressing structural drivers and more immediate medical needs, in combination with peer outreach, will lead to community empowerment and reduce FSWs’ HIV and STI incidence and behavioral risks.

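### Expanding the aim 1 behavioural model with follow-up homelessness and health-service use, which SPARC is meant to change, means its arm-by-time term no longer estimates the total intervention effect

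*Protocol article*

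**What the plan says.** All places are in the protocol article.

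- **Base model (Statistical Analysis).** The behavioural endpoints are analysed with a "random effect hierarchical logistic model, with the intervention indicator, time, and their interaction as the main explanatory variables". For imbalance between areas, "we will adjust for baseline confounding factors, including age, length of sex work, and number of sexual partners". The effect measure is the interaction: "The intervention effect will be assessed by comparing time trends in the intervention group with the time trend in the comparison group".
- **Expansion (same paragraph).** The model is then to be extended with further demographic variables, plus "time-dependent indicators of events such as arrest, homelessness, use of health services, or exposure to other prevention activities". The sentence closes with a qualifier about having no connection with the study. The expansion is stated as a commitment. The article does not call the expanded model secondary or exploratory, and does not say which model supplies the reported intervention effect.
- **What SPARC does.** Background lists biomedical and behavioural services and "structural (eg, financial literacy, legal aid, and housing referrals) services provided through SPARC". The section on the SPARC center describes on-site reproductive, sexual health and medication-assisted treatment clinics, and gives greater engagement in care as a purpose of the model.
- **Role of the indicators (Aims and Hypotheses).** Aim 2 follows change in structural vulnerability, with housing stability as a named example. Aim 3 examines "the role of these indicators as mediators of the intervention effect on study outcomes".
- **Table 1.** Housing stability and access to health services stand under the heading Confounders.
- **Incidence endpoint (Statistical Analysis).** The logistic model is unadjusted, then extended with baseline covariates. A more detailed analysis uses "Poisson regression models to allow for time-updated covariates measured over time", without naming those covariates.

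**The concern.** Aim 1 asks for the effect of SPARC on risk behaviour, which includes whatever SPARC achieves by housing women or bringing them into care. A follow-up value of homelessness or service use comes after exposure and, on the article's own theory, lies between exposure and outcome. Holding it fixed compares the arms as if SPARC had not changed it. The arm-by-time coefficient then leaves out that route.

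Conditioning on such a variable can also induce an association between arm and any unmeasured cause shared by that variable and the outcome. Neither effect is visible in the model output.

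At stake is interpretation. Two coefficients will exist, one from the base model and one from the expanded model. If the second is reported as the adjusted intervention effect, a real benefit that works through housing or care could look smaller than it is.

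**Working it through.** **1. The listed covariates against SPARC's stated role**

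| Time-dependent covariate | What the article says elsewhere | On the pathway? |
|---|---|---|
| Use of health services | Delivered at SPARC. Receiving medical care is named as an intervention component later in the same paragraph | Yes, directly |
| Homelessness | Housing referrals are a SPARC service. Housing stability is an aim 2 indicator, and aim 3 tests those indicators as mediators | Yes |
| Arrest | Legal aid is offered, and criminal justice involvement is a vulnerability reported from the earlier cohort. Fewer arrests is not a stated target | Indirect only |
| Other prevention activities | Described as unrelated to the study | No |

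**2. Which models are touched**

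- Base behavioural model: baseline covariates only. Not affected.
- Logistic incidence models: no covariates, or baseline covariates only. Not affected.
- Expanded behavioural model: affected.
- Poisson incidence model: covariates unnamed, so affected only if the same variables enter.

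**3. The plan's own effect size**

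The sample size section gives 83% power for an odds ratio (OR) of 0.50, with 20% control prevalence, n = 160 and 112, and rho = 0.2.

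- Intervention risk: odds 0.25 × 0.50 = 0.125, so 0.125/1.125 = 0.111.
- Multiplier for three follow-up visits: 3/(1 + 2 × 0.2) = 2.143, giving 112 × 2.143 = 240 and 160 × 2.143 = 343 effective observations.
- SE of the log OR: √[1/(240 × 0.20 × 0.80) + 1/(343 × 0.111 × 0.889)] = 0.236.
- Power: Φ(0.693/0.236 − 1.96) ≈ 0.837.

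The stated figure reproduces. It is used below only to take OR 0.50 and a 20% control risk as the reference total effect.

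**4. Illustration of direction and possible size**

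Inputs from the documents: control homelessness h₀ = 65.8% (106/161, Table 2), control outcome risk 20%, total OR 0.50. Assumptions: homelessness is the only mediator, there is no unmeasured confounding, and the contrast is at a single follow-up time. SPARC's OR on homelessness and the OR of homelessness on the outcome are also assumed.

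Method: find h₁, the intervention-arm homelessness. Find the stratum risks that average to 20% in control and 11.1% in intervention. The within-stratum OR is the adjusted effect.

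Worked case, SPARC OR on homelessness 0.50 and homelessness OR on outcome 2:

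- h₁: odds 0.658/0.342 = 1.924; × 0.50 = 0.962; h₁ = 0.962/1.962 = 0.490.
- Control: risks 0.133 (housed) and 0.235 (homeless). Check: 0.342 × 0.133 + 0.658 × 0.235 = 0.200.
- Intervention: risks 0.078 and 0.145. Check: 0.510 × 0.078 + 0.490 × 0.145 = 0.111.
- Adjusted OR = (0.0783/0.9217)/(0.133/0.867) = 0.554. Share of the log OR removed: 1 − ln(0.554)/ln(0.50) = 15%.

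| SPARC OR on homelessness | Adjusted OR (homelessness OR on outcome 1.5 to 4) | Share of log OR removed |
|---|---|---|
| 0.75 | 0.51–0.53 | 3–7% |
| 0.50 | 0.53–0.60 | 9–25% |
| 0.33 | 0.56–0.69 | 15–46% |

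Every cell moves toward the null. The upper end needs both assumed effects to be strong. Health-service use is not in this grid, and the documents offer no figure for it.

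**The case against.** **The effect models already use baseline covariates.** This stands. The base behavioural model and both logistic incidence models are specified as one would want, so the total effect remains estimable. What is missing is a statement that the base model is the one that answers aim 1.

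**The closing qualifier could cover the whole list.** The words about being unrelated to the study attach most naturally to other prevention activities only. Read more widely, they still do not help: the homelessness item in Table 1 asks whether it occurred in the past 6 months and cannot separate SPARC-related from unrelated changes.

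**In a nonrandomised comparison of city areas, follow-up adjustment has a rationale.** This is fair. Arrests or local services may shift between areas for reasons that have nothing to do with SPARC, and with repeated measures a variable can be both a mediator of earlier exposure and a confounder of later exposure. That justifies a supplementary model, but not reading its arm-by-time term as the total effect.

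**Table 1 may mean baseline values.** Plausible, since the article cites the table when describing the baseline survey. The heading needs clarifying; it is not shown to be wrong.

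**Stronger readings.** A reader might infer that the trial's main effect estimate is already biased, that the incidence analysis shares the fault, or that power falls well below 83%. The documents do not support these. The base models are clean, the Poisson covariates are unnamed, the mediated share is not given, and the power figure was not stated for the expanded model.

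**Conclusion.** The point holds for the expanded behavioural model. Follow-up homelessness and health-service use lie on SPARC's stated pathway, so the interaction term in that model is not the total effect named in aim 1. The shift is toward the null if SPARC improves these factors and they affect risk; bias from conditioning on post-exposure variables may add to or offset it.

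The size is unknown. The 3% to 46% range rests on assumed effects for a single mediator and shows only that the loss could be trivial or substantial. Arrest is a caution rather than a finding, and the Poisson model is implicated only if the same variables are entered. The practical risk is that, with no model named as the source of the aim 1 effect, the expanded coefficient is reported as the adjusted intervention effect.

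**What to change.** 1. State that the baseline-adjusted model (arm, time, interaction, baseline confounders) gives the aim 1 behavioural effect. Baseline homelessness, arrest history and service use may be added to it.
2. Take follow-up homelessness and health-service use, and as a caution arrest, out of that effect model. Use them only in the aim 2 and 3 models, or label any model containing them as exploratory and not an estimate of the total effect.
3. Apply the same rule to any such time-updated covariate in the Poisson model.
4. Make clear that the Confounders heading in Table 1 refers to baseline values.
5. Indicators of prevention activities unrelated to the study may stay.

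The cost is wording only. The baseline survey already covered arrest history and health-service use, and baseline homelessness is in Table 2, so no new data are needed.

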#### Cohort Study Target Population and Sample

Cohort participants were FSWs aged ≥18 years who live in Baltimore City; self-reported that they had traded sex for money, goods, or drugs 3 or more times in the past 3 months; and were not currently enrolled in our previous cohort study, the SAPPHIRE study [40]. Although transgender female sex workers (TFSWs) who reported being assigned male at birth were encouraged to visit the SPARC center and engage with peer outreach workers, they were excluded from the EMERALD study cohort because of a lack of comparable recruitment locations between the intervention and control areas.

Participants were assigned to a study arm based on the geographic location in which they were recruited. The initial target sample size was 350 women based on power calculations to observe a change in the intervention compared with the control group over the 3 follow-up visits. The assumptions used for the calculation were (1) n=200 in the intervention group and n=150 in the comparison group, (2) lost-to-follow-up (LTFU) rate of 10% to 20% in the intervention (effective n=160-180) and LTFU of 20% to 25% in the comparison group (effective n of 120-112), (3) intraperson correlation (Rho)=0.2-0.4, (4) varying levels of baseline risk behavior rate, and (5) a 2-sided α=.05. Thus, assuming effective sample sizes of n=160 in the intervention and n=112 in the comparison groups, the power is 83% to detect an odds ratio of 0.50, assuming a 20% prevalence rate of a risk behavior (eg, drug use) in the control group and an intraperson correlation of Rho=0.2. For the cumulative incidence outcome, with an average N contributing to the analysis of 170 in the intervention and 120 in the control groups, and assuming annual incidence rate of 6%, the power is 80% to detect a rate ratio of 0.28.

The enrollment target was increased to 450 midway through data collection after power calculations were reassessed based on actual retention rates within the sample, which were closer to 65%. The LTFU rate was higher than anticipated based on previous studies [41], likely because of high incarceration rates, the mobility of the population, and the length of time between study visits (6 months). Although we aimed for a sample of 450 participants, recruitment was stopped at 385 because of reaching saturation in the recruitment areas and repeatedly encountering participants attempting to reenroll in the study.

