#### Cohort Retention Methods

Follow-up visits for EMERALD occurred at 6, 12, and 18 months after the initial baseline interview. Participants received US $40 prepaid Visa debit cards for completing each follow-up visit. Participants were eligible to complete each follow-up visit 1 month before their actual interview date until 1 month after, for a total eligibility window of 2 months. Those who failed to complete an interview within the allotted eligibility window were considered lost to follow-up. Participants who missed a visit could still complete their next scheduled visit and were not withdrawn from the study.

Retention protocols were modeled after strategies used in SAPPHIRE [50] and are more fully described in a study by Silberzahn et al [41]. Briefly, retention strategies consisted of the aforementioned locator forms (eg, phone numbers, addresses, and social media accounts); promotional materials (eg, hand sanitizer, wipes, lip balm, and silicon bracelets) branded with the study logo and phone number; monitoring public information databases to determine if participants were incarcerated, had moved, or were deceased; and outreach in the form of phone calls, social media messaging, home visits, and repeated visits to recruitment areas in both the study RV and a study sedan, which was used for follow-up. The study team also relied on tracking teams of 2 study staff who were assigned participants to focus on with 1 month of eligibility remaining.

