Building on the strategies used in SAPPHIRE, the EMERALD cohort retention protocols were enhanced using several additional strategies. A password-protected database was developed to monitor follow-up and participant progress during the study visits. Using this database, study management could easily determine current and projected follow-up rates, the number of participants due for a study visit (6, 12, and 18 months), and all previous contact attempts used to locate a participant. Field staff documented how participants were located (eg, phone calls and home visits) and time spent on van shifts and tracking, which allowed study management to determine adequate staffing and consider the best follow-up strategies. For example, study staff could monitor the number of difficult-to-reach participants due for follow-up surveys in specific study areas and direct tracking teams to these locations to increase the probability of chance encounters with participants. Additionally, check-in locator visits were conducted in between formal study visits at 3, 9, and 15 months to touch base with participants and inquire about any changes to contact information on file (eg, phone numbers, addresses, family and friends). Finally, although SPARC staff were prohibited from discussing the EMERALD study with clients, participants could obtain the EMERALD study phone number from SPARC center administrative staff at their request and use the SPARC office phone to contact the EMERALD study staff, determine follow-up eligibility, and schedule follow-up interviews.

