### Limitations

Despite successful implementation and the novelty of this intervention in a US setting, we encountered several challenges throughout this study. Although TFSWs experience disproportionately high rates of victimization and are underrepresented in research, a lack of comparable recruitment locations in the intervention and control areas prohibited the inclusion of TFSWs in our study [63,64]. In addition, the onset of the COVID-19 pandemic in March 2020 required adaptations to service provision and data collection. In-person services at the SPARC center were stopped on March 17, 2020. However, because the framework was already in place, the SPARC team was able to quickly pivot to an all-outreach service model when the COVID-19 pandemic forced the closure of the drop-in center.

Regarding the EMERALD evaluation, data collection for the cross-sectional survey was paused at the onset of the COVID-19 pandemic, and data collection was shifted to a telephone format for the remaining 18-month surveys. As a result, we were unable to conduct HIV and STI testing for 27 participants. We plan to reopen in-person services at the SPARC center, resume the 96 in-person cross-sectional surveys, and complete the 19 remaining in-depth interviews when data collection with human subjects is deemed safe and appropriate.

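### The lead analysis of HIV and STI incidence takes no account of how often each woman was tested, so any difference in testing between arms would distort it

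*Protocol article*

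**What the plan says.** The Statistical Analysis section of the protocol article names HIV and STI incidence as the primary biological endpoint. It says "we will initially estimate cumulative incidence rates in both the intervention and comparison participants as a binary outcome", and the intervention effect is "assessed using an unadjusted random effect logistic model, with the intervention indicator as the only explanatory variable". The next step adds baseline covariates. After that, "A more detailed analysis will employ person-time methods with Poisson regression models", with the rule that "Those lost to follow-up will contribute time-at-risk until the time of their last visit".

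Four other places bear on this:

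- Cohort Study Target Population and Sample assumes 10 to 20% loss in the intervention group and 20 to 25% in the comparison group. It later refers to "actual retention rates within the sample, which were closer to 65" per cent, for the whole sample only.
- Cohort Retention Methods states: "Participants who missed a visit could still complete their next scheduled visit and were not withdrawn from the study".
- The same section lets participants, at their request, "use the SPARC office phone to contact the EMERALD study staff".
- Limitations reports that after 18-month surveys moved to telephone, "we were unable to conduct HIV and STI testing for 27 participants".

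**The concern.** Study testing takes place at baseline and at 6, 12 and 18 months, so a follow-up infection enters the endpoint only if a test is done. A yes/no outcome with arm as the sole term gives a woman with one negative test the same weight as a woman with three. Adding baseline covariates does not bring in the number of tests or the length of follow-up.

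This matters only if testing differs between arms. The plan's own loss assumptions differ by arm. Only women from the intervention area were encouraged to visit SPARC, so its telephone is a plausible arm-linked route to better retention. If the intervention arm was tested more, its cumulative incidence would be inflated relative to control and a real benefit could be partly hidden.

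The person-time analysis is better placed, but it comes later in the sequence. Its stopping rule also counts untested time when a visit is skipped, or when a telephone survey is taken as the last visit.

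**Working it through.** **Inputs from the article.** Three follow-up tests. Planned loss of 10–20% and 20–25% gives midpoint attendance of 85% and 77.5%, a widest gap of 90% against 75%, and ranges that touch at 80%. The article's effective sample sizes follow from these losses: 200 × 0.80 to 0.90 = 160 to 180, and 150 × 0.75 to 0.80 = 112.5 to 120. Its power figures do not enter this check.

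**Assumptions.** The true risk is 8% per six-month interval in both arms (no effect). For scale, the earlier cohort's 12-month incidences of 13.7% and 18.2% convert to 1 − √0.863 = 7.1% and 1 − √0.818 = 9.6% per interval. Planned loss is read as the chance of missing each visit, independently, so attendance per visit is *r*.

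**Binary outcome, infection visible only at the visit closing its interval (transient).** P = 1 − (1 − 0.08*r*)³.
- 85% vs 77.5%: 1 − 0.932³ = 0.1904 and 1 − 0.938³ = 0.1747. OR = (0.1904/0.8096)/(0.1747/0.8253) = 1.11.
- 90% vs 75%: 1 − 0.928³ = 0.2008 and 1 − 0.940³ = 0.1694. OR = 1.23.

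**Binary outcome, infection visible at any later test (persistent).** P = *r*(1 − 0.92³) + *r*(1 − *r*)(1 − 0.92²) + *r*(1 − *r*)²(0.08).
- 85% vs 77.5%: 0.2092 and 0.2014, OR 1.05.
- 90% vs 75%: 0.2137 and 0.1985, OR 1.10.

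**Only women tested at least once.** Divide each P by 1 − (1 − *r*)³, which is 0.9966, 0.9886, 0.9990 and 0.9844 for 85%, 77.5%, 90% and 75%.

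| Null odds ratio, intervention to control | 85% vs 77.5% | 90% vs 75% | 80% vs 80% |
|---|---|---|---|
| Transient, all enrolled | 1.11 | 1.23 | 1.00 |
| Transient, tested at least once | 1.10 | 1.21 | 1.00 |
| Persistent, all enrolled | 1.05 | 1.10 | 1.00 |
| Persistent, tested at least once | 1.04 | 1.08 | 1.00 |

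**Sensitivity.** Over annual incidence of 6% to 18.2%, the transient, all-enrolled odds ratio at 90% vs 75% is 1.21 to 1.24. If losses are permanent dropout instead (90% vs 75% still in the study at 18 months), it is 1.14 to 1.16.

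**Person-time to last visit.** Expected intervals to the last visit are 3*r* + 2*r*(1 − *r*) + *r*(1 − *r*)²: 2.824 (85%), 2.713 (77.5%), 2.889 (90%) and 2.672 (75%). Tested intervals are 3*r*: 2.55, 2.325, 2.70 and 2.25.
- Transient infection with skipped visits: the null rate ratio is (2.55/2.824)/(2.325/2.713) = 1.05, and (2.70/2.889)/(2.25/2.672) = 1.11.
- Persistent infection: 1.00 to 1.01.
- Permanent dropout unrelated to risk: 1.00.

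**Counting only intervals that end in a test.** Transient infection gives 1.00. Persistent infection gives roughly the reciprocal of the figures above, 1/1.05 = 0.95 and 1/1.11 = 0.90, because events from skipped intervals are kept and their risk time is dropped. That error favours SPARC.

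**The case against.** The strongest reply has four parts.

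- **Unequal testing is not shown.** The loss ranges are power assumptions that touch at 20%, and observed retention overtook them. That retention is given for the whole sample only. A reader might infer that the intervention arm was in fact tested more, but no section reports this. This stands.
- **The telephone was not aimed at one arm.** SPARC staff were barred from discussing the study, the telephone was available on request, and nothing in the article stops control women from using it. The other retention methods are described without distinction by arm. This stands: the telephone is a plausible route to a difference and no more.
- **The direction is not fixed.** A reader might infer that the result must be biased against SPARC. That requires missed tests to be unrelated to risk. The article attributes loss partly to incarceration and mobility, and SPARC offers STI testing and treatment between visits. Either could push the comparison up or down. This stands.
- **A person-time analysis is already planned, and an article leaves detail to the full plan.** This stands in part. How untested women enter the denominator is such a detail, and the table therefore shows both options. The binary outcome and the arm-only model are stated choices, however, and the person-time model comes after them as a more detailed analysis. Its rule is sound for permanent, non-informative dropout and nearly so for persistent infection. It is not sound for infections that clear when visits are skipped.

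**Conclusion.** The point holds as a conditional one. The stated lead comparison for the primary biological endpoint does not adjust for testing opportunity, in a cohort with about 35% loss, intermittent attendance and 27 women without testing at 18 months. With no true effect, the differences in loss that the plan itself assumed would give an odds ratio of about 1.04 to 1.11 at their midpoints and about 1.08 to 1.23 at their widest. The spread depends on whether infections persist and whether untested women are counted. These figures rest on an assumed 8% risk per interval, independent misses, and missingness unrelated to risk. They are not estimates of bias in the observed data, because testing by arm is unknown. Equal testing gives no distortion.

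**What to change.** - Make the already planned person-time or interval-based model the primary biological analysis, and label the binary logistic model descriptive.
- End time at risk at the last completed test instead of the last survey visit, so that the telephone-only 18-month visits add no untested time.
- Analyse HIV separately, using time since the last negative test, because antibody found at a later test can reflect infection in a skipped interval.
- For chlamydia and gonorrhea, run two definitions of time at risk as bounding analyses: tested intervals only, and time to last test. The first is biased if infection persists, the second if it clears.
- Report retention and tests per woman by arm, and add inverse-probability-of-testing weights as a sensitivity analysis.

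The change should be written down and dated before outcomes are compared by arm. It costs analysis wording and code and a little simplicity, with no new data.
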